## Abstract

**Background:**

Dysphagia is a common and serious complication after (chemo)radiotherapy (CRT) for head-and-neck cancer (HNC) patients. Prophylactic swallowing exercises (PSE) can have a significantly positive effect on post-treatment swallowing function. However, low adherence rates are a key issue in undermining this positive effect. This current randomized trial will investigate the effect of adherence-improving measures on patients’ swallowing function, adherence and quality of life (QOL).

**Methods:**

This ongoing trial will explore the difference in adherence and swallowing-related outcome variables during and after PSE in HNC patients performing the same therapy schedule, receiving different delivery methods. One hundred and fifty patients treated in various hospitals will be divided into three groups. Group 1 performs PSE at home, group 2 practices at home with continuous counseling through an app and group 3 receives face-to-face therapy by a speech and language pathologist. The exercises consist of tongue-strengthening exercises and chin-tuck against resistance with effortful swallow. The Iowa Oral Performance Instrument and the Swallowing Exercise Aid are used for practicing. Patients are evaluated before, during and after treatment by means of strength measurements, swallowing and QOL questionnaires.

**Discussion:**

Since low adherence rates undermine the positive impact of PSE on post-treatment swallowing function, there is need to develop an efficient PSE protocol maximizing adherence rates.

**Trial registration:**

ISRCTN, ID: ISRCTN98243550. Registered retrospectively on 21 December 2018.

## Background

Dysphagia is a common and widely reported complication after (chemo)radiotherapy (CRT) for head-and-neck cancer (HNC) patients and can persist for a long period of time [1–5]. Fifty to 60% of the HNC patients undergoing CRT may experience significant post-treatment dysphagia involving both muscle weakness and incoordination/timing issues [6–8]. The medical consequences (e.g., feeding-tube dependency, malnutrition, aspiration pneumonia) have a major negative impact on daily functioning and health-related quality of life (QOL) and can even be life-threatening [9–15]. These consequences and the high prevalence of swallowing disorders in HNC patients stress the importance of prevention, monitoring and management of this problem [16].

Based on literature and clinical experiences, it can be concluded that nowadays there is no “gold-standard” in the assessment or treatment of dysphagia in HNC patients [17, 18]. An increasing number of studies show that prophylactic swallowing exercises (PSE) can have a significantly positive effect on post-treatment swallowing function, can lead to significantly less muscle atrophy and can improve dysphagia-related QOL in HNC patients treated with CRT [7, 19–24]. However, low adherence rates are a key issue in undermining these positive effects. Reported adherence rates, with adherence defined as “the extent to which patient behavior corresponds with recommendations from a health care provider,” range from 13 to 64% [21, 25–31]. A possible reason for low adherence rates is the additional demand that PSE programs put on the patient, during an already burdensome period [20]. Furthermore, Shinn et al. [25] and Wells and King [30] showed that the etiology can be multifactorial; e.g., forgetting, absence of supervision or the fact that patients do not experience the problem at the start of the exercises.

The indications that PSE can improve patients’ swallowing function and swallowing-related QOL show the crucial, urgent and internationally recognized need for an effective PSE program augmented with measures that may add to adherence [7, 19–25, 27]. Apart from patient characteristics and disease-related aspects, several studies show the impact of different measures on adherence: therapist-supervised exercises, regular counseling and reinforcement sessions, clear and repeated instructions, feedback on successful performance, target setting (e.g., number of repetitions/days) and limited duration [7, 27, 30, 32, 33]. Also, therapist supervision and a close relationship with a therapist play a crucial role in patients’ satisfaction, compliance and individual beliefs in personal skills [30].

Up to now, studies comparing standard PSE with a PSE program augmented with adherence-improving measures are lacking. The randomized controlled trial (RCT) of Wall et al. [26] included 79 patients and investigated whether therapy adherence to prophylactic swallowing exercises was influenced by the delivery method of the exercises. Three different methods were compared. The first group received face-to-face therapy by a speech and language pathologist (SLP), the second group used a telepractice application and the third group practiced independently at home. Adherence was calculated based on the completion of all prescribed exercises. Significantly better adherence rates were found in the group receiving face-to-face therapy and a trend towards better results was found in the group using the application.

This current multicenter randomized trial will investigate the effect of adherence-improving measures on actual patient compliance, swallowing function and QOL. Patient adherence to a prophylactic swallowing-therapy protocol will be examined across three models, similar to the delivery methods in the RCT of Wall et al.: (1) self-help standard PSE (control group), (2) self-help app-supported PSE (app group) and (3) a SLP-supported PSE (therapist group). Our study differs from the above-mentioned study in the type of exercises given, the number of patients included and the adherence-specific measures. The goal of the proposed randomized trial is to develop an optimized PSE program, incorporating patient tolerance and support for the exercise program. The findings of this project should be helpful in setting up future guidelines and directions. The final patient benefit will be improved swallowing function and QOL.

This study aims to
Conduct a prospective randomized trial investigating the effect of specific adherence measures on patients’ actual compliance, wellbeing, muscle strength, swallowing function and QOL during and following CRTIncrease insight in the underlying reasons for (non- )adherence in this patient population

## Methods

### Study population

Patients with a stage III or IVA-B (TNM7) newly diagnosed squamous cell carcinoma of the oropharynx are considered as possible participants. Inclusion criteria are: patients treated with radiotherapy or concomitant CRT (CCRT) with or without induction chemotherapy and demonstrating sufficient cognitive and language abilities. The presence of a recurrent carcinoma or metastasis from another carcinoma and previous CRT or surgery in the head-neck region, with possible impact on swallowing function, are exclusion criteria. The patients will be recruited by a radiation oncologist and SLP. The SLP explains the study protocol and study design and assigns participants to the interventions.

### Minimization

All subjects who give consent for participation and who fulfill the inclusion criteria are randomly assigned to one of the three groups with a 1:1:1 allocation by means of the program QMinim. It is an online minimization service supported by the Information and Communication Technology (ICT) Unit of the Antwerp University Hospital. Minimization factors are age (20–60 years vs. ≥ 60 years), treating center, presence of baseline dysphagia and treatment (radiotherapy vs. CCRT).

As this is an open-label trial, the minimization procedure and outcome assessment will not be blinded.

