#### Data analysis

Patients will be analyzed in the groups to which they are assigned (intention-to-treat). Descriptive statistics will be used to summarize patient characteristics per treatment group. Data will be analyzed using linear mixed-effects models with group, time and group by time interaction as fixed effects. A random intercept will be added to account for correlation between measurements coming from the same individual. When one or more overall effects are significant, post-hoc pairwise testing with Bonferroni-Holm correction for multiple testing will be performed. Missing data is assumed to be missing at random (MAR) and, thus, will be ignored in the analyses. By using mixed-effects models for the analysis, we can incorporate all information on the available time points. If more than 15% of the data is missing, a sensitivity analysis will be conducted by using multiple imputation. Results of the original analysis of the available cases will be interpreted in the context of sensitivity analysis.

Additionally, the impact of adherence, HPV status, dosimetry and mucositis on the different functional endpoints will be studied in exploratory linear mixed-effects models. Fixed main-effects and interactions with group for all these factors will be evaluated.

More details on the primary, secondary and exploratory analyses can be found in the statistical analysis plan.

A *p* value of less than 0.05 will be considered statistically significant. All analyses will be conducted using SPSS Statistics version 25 (IBM, Chicago, IL, USA) and R software (R Foundation, Auckland, New Zealand).

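### The primary model omits the four minimisation factors, which makes the group and visit-level tests conservative, and the group-by-time test too if the factors alter the course of MASA-C

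*Protocol article*

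**What the plan says.** Under Minimization, patients are "randomly assigned to one of the three groups with a 1:1:1 allocation by means of the program QMinim". The factors are age group, "treating center, presence of baseline dysphagia and treatment (radiotherapy vs. CCRT").

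Under Data analysis, the model is fixed as "linear mixed-effects models with group, time and group by time interaction as fixed effects". The only random term is for the patient: "A random intercept will be added to account for correlation between measurements coming from the same individual". None of the four factors and no centre term is listed. The exploratory models bring in other covariates ("the impact of adherence, HPV status, dosimetry and mucositis on the different functional endpoints will be studied in exploratory linear mixed-effects models"), and none of these is a minimisation factor.

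Testing then runs through overall effects to pairwise comparisons: "When one or more overall effects are significant, post-hoc pairwise testing with Bonferroni-Holm correction for multiple testing will be performed". The group main effect, the group-by-time interaction and the pairwise contrasts are therefore all part of the inference. The sample size section powers the trial for a different evolution of MASA-C over time, which is the group-by-time test.

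Further detail is deferred: "More details on the primary, secondary and exploratory analyses can be found in the statistical analysis plan". That plan is not shown.

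**The concern.** Minimisation makes the arms more alike on the chosen factors than chance would. If those factors predict the outcome, the true sampling variation of a between-arm difference is smaller than under simple randomisation. A model without the factors does not know this: it estimates the standard error as if the balance had been left to chance. Standard errors then come out too large, p-values too high and intervals too wide.

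At stake are precision and power in a trial planned for 80% power, whose pairwise comparisons also carry a Holm correction. Differences between RT and CCRT in how far swallowing declines are plausible. So are differences between centres in scoring, since outcome assessment is unblinded and done by speech and language pathologists in several hospitals.

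**Working it through.** **1. The plan's own figure.** Inputs from Sample size calculation: baseline mean 195; later means 171, 177 and 180, constant after 6 weeks; SD 11; base correlation 0.4 with decay rate 0.5; four time points; alpha 0.05. Read in the usual base-plus-decay form with equally spaced visits, the correlations are 0.4, 0.4^1.25 = 0.318 and 0.4^1.5 = 0.253. Simulating the Geisser-Greenhouse-corrected group-by-time test (6,000 runs) at 37 per group gives power 0.81–0.815, or 0.80 with visits at 0, 6, 10 and 18 weeks. The stated 0.80 is reproduced. For dropout, 1 − 111/150 = 26%, which agrees with the stated allowance of more than 20%.

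**2. What theory predicts for one contrast.** Suppose the factors explain a share R² of the variance of a contrast and are perfectly balanced. A nominal two-sided 5% test then has true error 2 × [1 − Φ(1.96/√(1 − R²))], and its interval is too wide by 1/√(1 − R²) − 1.

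| R² | true error | excess width |
|---|---|---|
| 0.1 | 3.9% | 5% |
| 0.2 | 2.8% | 12% |
| 0.3 | 1.9% | 20% |

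This applies directly to a two-arm comparison at one visit.

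**3. Group main effect.** This test averages over visits, which shrinks within-patient noise but not a constant factor effect. The mean correlation over the 4 × 4 matrix is [4 + 2(3 × 0.4 + 2 × 0.318 + 0.253)]/16 = 0.511. If the factors explain 20% of the variance at each visit, their share of the patient mean is 0.2/(0.2 + 0.8 × 0.511) = 0.33. For a 2-df test under perfect balance, the large-sample error is 0.05^(1/(1 − 0.33)) ≈ 1.2%. The main effect is hit harder than a single-visit contrast.

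**4. Simulation of the actual design.** Pocock-Simon minimisation, three arms, 111 patients, no treatment effect, 2,000–3,000 runs per scenario. Assumptions not in the article: 3, 5 or 10 centres; 30% with baseline dysphagia; 70% CCRT; 50% aged 60 or over; assignment probability 0.8 or 1.0; factors explaining 20% of variance. In the adjusted analysis all four factors enter, and all four interact with time in the group-by-time test. Pairwise figures are for the last visit, before Holm.

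Rejection rate at nominal 0.05:

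| Test | without factors | with factors |
|---|---|---|
| *Factor effects constant over time* | | |
| Group main effect | 0.015–0.018 | 0.046–0.056 |
| Pairwise | 0.026–0.039 | 0.046–0.058 |
| Group by time | 0.037–0.055 | 0.041–0.056 |
| *Factors change the post-baseline decline* | | |
| Group main effect | about 0.025 | 0.044–0.050 |
| Pairwise | 0.032 | 0.054 |
| Group by time | about 0.030 | 0.045–0.051 |

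At 150 patients the pattern is the same. With constant effects explaining 10% or 30% of variance, the unadjusted main-effect test rejects 0.029 or 0.005. Under simple randomisation with 20%, it rejects 0.051, so the distortion comes from analysing minimised data without the factors.

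**5. Power of the targeted test.** Under the article's assumed means, with factors that change the decline, group-by-time power is 0.85 without the factors and 0.89 with factor-by-time terms (1,500 runs). With constant factor effects explaining 20%, it is 0.887 in both analyses.

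**The case against.** The strongest objection is that the test the trial is powered for is group by time. A factor that shifts a patient's score equally at every visit cancels out of within-patient change, because the patient intercept absorbs it. The simulation confirms this: with constant effects, that test is unaffected. This stands, and it limits the point.

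Second, a condensed article often leaves adjustment covariates to the SAP, and the article refers to one. This stands in part. It cannot be said that the trial's final analysis will omit the factors. But the article does not stay silent: it lists the fixed and random effects, and that list does not match the allocation. If the SAP does include the factors, the article misdescribes the primary model.

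Third, the size depends on prognostic strength, for which the article gives no figure. This stands, and every figure on size is conditional on it.

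Three stronger readings are tempting and are not supported:
- *That a fifth of the patients are wasted if R² is 0.2.* For the powered test the loss is nil when factor effects are constant. When the factors change the decline, power of 0.85 against 0.89 converts, through the F-test noncentrality with 2 to 6 numerator df, to about 10–11% of effective sample size.
- *That ignoring centre-level correlation is a further harm.* Centre is itself a minimisation factor, so this is the same conservative effect counted twice.
- *That the p-values are anti-conservative.* No scenario shows rejection above the nominal level beyond simulation error.

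**Conclusion.** The point holds as a mismatch between design and stated analysis that costs efficiency. It does not invalidate the inference, and the stated sample size is not wrong on this account.

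The group main-effect and visit-level pairwise tests, both in the stated testing scheme, are conservative if the factors predict MASA-C after baseline. The group-by-time test is conservative only if the factors modify its course. At an assumed 20% of variance explained, true error is roughly a third of nominal for the main effect, and between half and four-fifths for a pairwise test. For group by time it is about three-fifths, in the effect-modifying case only. If the factors explain nothing, nothing is lost.

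A reader might infer from the article that the final analysis certainly leaves these factors out. The unseen SAP prevents that conclusion. What can be said is that the model printed in the article does so.

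**What to change.** Add age group, treating centre, baseline dysphagia and RT vs CCRT as main effects to the primary and secondary mixed models. Centre can be a random effect, or fixed with small centres merged by a rule set in advance. Add RT/CCRT by time and baseline dysphagia by time as well, because main effects alone leave the group-by-time test unchanged. The adjusted group-by-time figures above come from letting all four factors interact with time, so two interactions recover only the part that those two factors carry.

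The cost is wording and some degrees of freedom; the data are already collected for allocation. With categorical time, two binary factors by time use 2 × (4 − 1) = 6 df over the four time points of the sample size calculation. Over all eight assessments (baseline, four weekly, end of CRT, 1 and 3 months) they use 2 × (8 − 1) = 14. The main effects and centre come on top.

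State the same model in the SAP before analysis. If the SAP already contains these factors, reconcile the Data analysis section of the article with it.

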### Study design

The study will be a multicenter RCT. All patients will be training five times a week during the first 4 weeks of CRT. Baseline measurements will be done before the start of CRT. Every week during the training, immediately after CRT and at 1 and 3 months following treatment, patients will be evaluated by radiation therapists and SLPs. Table 1 shows an overview of the study visits and evaluations during the study. Prophylactic swallowing exercises are the same in all groups and comprise evidence-based exercises targeting the main muscle groups involved in swallowing; namely, muscles involved in tongue strength, pharyngeal contraction and laryngeal elevation/upper esophageal sphincter opening. These strengthening exercises include tongue-strengthening exercises (TSE) and chin-tuck against resistance (CTAR) combined with an effortful swallow. First, TSE will be performed since tongue strength is the main bolus-driving force and reduced tongue strength can cause oral and pharyngeal residue and aspiration [34–36]. Second, CTAR exercises are used since they have a significant impact on the suprahyoid muscles, with a positive effect on laryngeal elevation and upper esophageal sphincter opening [37, 38]. The third exercise consists of effortful swallows in combination with the chin-tuck. Effortful swallows have been shown to improve the tongue-base posterior motion and can increase tongue-base pharyngeal-wall pressures [39]. It is hypothesized that the chin-tuck in combination with an effortful swallow stimulates the pharyngeal musculature [38].

**Table 1 Tab1:** Study visits and evaluations

			Study period				
	Enrollment	Allocation	Post allocation				
Time point	*Pre RT*	*Between enrollment and start RT*	*Weeks 1–4 of RT*	*Weeks 5–7 of RT*	*End of RT*	*1 month after RT*	*3 months after RT*
Enrollment:							
Eligibility screen	X						
Informed consent	X						
Allocation		X					
Interventions:							
*PSE – control group*			X				
*PSE – app group*			X				
*PSE – therapist group*			X				
Assessments:							
*Patient, disease and therapy characteristics*	X						
*Swallowing function*	X		X		X	X	X
*Muscle strength*	X		X		X	X	X
*Impact of mucositis*	X		X		X	X	X
*Quality of life*	X				X	X	X
*Attitudes towards exercises*			X				
*Overall fatigue*	X		X				

*RT* radiotherapy, *PSE* prophylactic swallowing exercises

The different exercises described above alternate during the sessions: all subjects start their first session with TSE and perform CTAR exercises and effortful swallowing in the next session. Tongue-strengthening exercises consist of 120 tongue presses and are divided into 12 sets of 10 repetitions with a 30-s rest between sets and with the target level set at 80% of 1 repetition maximum (1RM, i.e., the maximum amount of pressure that can be generated in one repetition) [34, 40–44]. The next session CTAR exercises and effortful swallows are performed. Each CTAR session consists of 150 chin-tucks against resistance at a target level of 60–70% [45] of the 1RM (i.e., in this study, the maximum chin-tuck strength that can be generated). These chin-tucks are divided into 30 sets of five repetitions with an effortful swallow at every fifth repetition. In both tongue and chin-tuck exercises, a successful repetition was defined as reaching the target level and holding the contraction for 3 s, using the green light (TSE) as biofeedback or tactile biofeedback (CTAR). According to the principle of progressive overload, maximal tongue strength and strength of the suprahyoid muscles and correspondent levels of resistance are measured at baseline and recalculated subsequently every week [44].

All subjects will be randomly assigned into the previously defined groups: control group, app group and therapist group. The groups differ in degree and kind of adherence-improving measures. All groups have some of these measures in common. Restricting the duration to the first 4 weeks of CRT is a first method to increase compliance since the literature shows that in the last 2–3 weeks of therapy the feasibility of completing exercises decreases [20, 33]. Receiving visual and tactile feedback on their performance via the therapeutic devices is a second method. The differences in adherence-improving measures between the groups are illustrated in Table 2. The first group (control group) will perform the exercises at home, without supervision of a SLP but with a counseling session of 10 min every week. Group 2 (app group) practices at home but receives continuous counseling and gets instructions by videos via an application on a tablet, developed in collaboration with Cyborn, Antwerp, Belgium (www.cyborn.be). Generally, mobile health applications are considered to be possible tools to improve traditional health care [46]. By means of gamification, the app helps, supports and motivates the patients to practice. The app registers when the patients practice, how many repetitions they do and when they succeed in doing the exercises. Group 3 (therapist group) is given face-to-face therapy and will be counseled by a SLP five times per week. All patients will complete the first session with supervision of the SLP, irrespective of their group. The intervention will be discontinued on participant request or in case of worsening disease, requiring major changes in treatment. Reasons for discontinuing will be stored in a database.

**Table 2 Tab2:** Study design

Inclusion	*n* = 150		
Stratified randomization	*n* = 50 Control group	*n* = 50 App group	*n* = 50 Therapist group
Therapy schedule	• 5x/week (30–40 min)	• 5x/week (30–40 min)	• 5x/week (30–40 min)
	• 4 weeks	• 4 weeks	• 4 weeks
	• Home practice	• Home practice but app-supported	• Therapist supervised
Exercises	• TSE	• TSE	• TSE
	• CTAR	• CTAR	• CTAR
	• Effortful swallow	• Effortful swallow	• Effortful swallow
Adherence measurements			
• Supervision	No (home practice)	No (home practice – app)	Yes (face-to-face therapy)
• Counseling	Counseling 1x/week by SLP (10′)	Counseling 1x/week by SLP (10′) & continuous counseling via app	Counseling by SLP 5x/week
• Feedback on performance	Yes – instrumental	Yes – instrumental	Yes – instrumental & by SLP
• Clear and repeated instructions	• Introduction session • Written instructions	• Introduction session • Instructions via app: animation videos	• Each session by the SLP
• Target setting	Yes	Yes	Yes
• Limited duration	Yes – first 4 weeks of CRT	Yes – first 4 weeks of CRT	Yes – first 4 weeks of CRT

*TSE* tongue-strengthening exercises, *CTAR* chin-tuck against resistance, *SLP* speech and language pathologist, *CRT* (chemo)radiotherapy

